### Follow-up & drop out

Baseline data will be collected by local PIs. Follow-up data will be collected by local PIs or research staff in each centre, or network research staff. For units in Wales this will be the Clinical Studies Officers employed by National Institute for Social Care and Health Research Clinical Research Collaboration (NISCHR CRC), in England the research nurses employed by the Comprehensive Local Research Networks (CLRN). The follow-up visits will be completed in the participants’ home or at a location of the participants’ choice. The follow-up appointments are timed to occur at important milestones both pre and postnatally: 36 weeks gestation, 6 weeks postpartum, 6 months postpartum and 12 months postpartum.

Every effort will be made to reduce loss to follow-up: women will be visited at a convenient location of their choice for all follow-up appointments. In order to improve response rates, participants will be contacted to rearrange any missed follow-up appointments, participant-nominated contacts will be collected at baseline in order to facilitate contact at follow-up appointments, participants will be posted study updates in the form of newsletters and follow-up calendars, and each participant will be provided with a £10 high street voucher as a thank you for completing each follow-up. A HELP study website will be used to provide study updates (http://medicine.cf.ac.uk/help-study/), and a minimum dataset will be developed to collect follow-up data by telephone for those participants who are unwilling or unable to meet with the researcher.

In order to prevent resentful demoralisation in the control group, each of these women will be offered 12 weeks normal community-based Slimming World sessions free of charge after her 12 month follow-up is complete. Any woman who undergoes a miscarriage, stillbirth, neonatal death or termination of pregnancy will be given an open option whether or not they wish to continue participation in the study.

All site study staff including the Intervention Midwife and Slimming World consultant will be visited by the research team and updated via regular contact and newsletters in order to encourage continued enthusiasm. In addition, to prevent disappointment following randomisation in the control sites, if results from the study prove positive units allocated to the control group will then be offered training for their midwives in the intervention.

### Process evaluation

A process evaluation will be conducted in line with the framework suggested by Steckler and Linnan [95]. This evaluation will utilise both qualitative and quantitative data including data taken from focus groups, interviews, site intervention group observations, session summaries. The process evaluation model will include assessment of eight components; these are context, reach, exposure, fidelity, recruitment, retention, contamination and theory testing. The definition of some of these elements is less clear than others and there is some overlap between concepts, so these are defined here as used in this study. “Context” includes information relating to different aspects of the context that the intervention was delivered in. This was explored by addressing who delivered the intervention and where it was delivered. The broader context was considered in the qualitative work and includes data on circumstances, skills, resources and attitudes that may influence intervention effectiveness. “Reach” is defined as the extent to which the target audience is reached by the intervention as well as whether the intervention had ‘spillover’ effects on other people not recruited in the trial. We were interested in exploring whether it had any impact on the family and friends of the participants. “Exposure” is defined as whether the participants received the different elements of the intervention and whether the participants implemented the different elements as intended. “Fidelity” is defined as the degree to which the Intervention Midwives and Slimming World consultants delivered the intervention as intended.

We will assess study attrition by intervention or control group as well as by site. We will compare those dropping out with those remaining in the trial in terms of demographics. We will attempt to obtain reasons for dropout where possible and record these. Finally, we will assess potential contamination between groups through the interviews and focus groups as well as by obtaining details of all other services or interventions that control group participants accessed. Table 3 shows the key sources of information used to explore the eight components of the process evaluation.

**Table 3 T3:** Process Evaluation Elements

**Process evaluation component**	**Assessment**
Context	• Data collected on a site proforma detailing site demographics, ethnicity, size, services delivered etc.
	• Data on those delivering the intervention
	• Data from two site observations completed at different time points in the intervention delivery period using a structured observation guide.
	• Contextual issues explored in the staff focus groups and participant interviews
Reach	• Attendance at the group sessions
	• Comparison of characteristics of those attending the intervention with those not attending
	• Reach explored in the staff focus groups and participant interviews
Exposure	• Number of group sessions delivered
	• Data from group session summary forms which describe those attending and the content/timings of sessions
	• Data from site observations (two per site)
	• Attendance at group sessions
	• Exposure and attendance explored in the staff focus groups and participant interviews
	• Data gathered on use of pedometers, step targets and walking diary completion
Fidelity	• Data from site observations (two per site)
	• Data from group session summary forms which describes how the intervention was implemented at each session
	• Fidelity explored in the staff focus groups and participant interviews
Recruitment	• Comparison of demographics of sites recruited
	• Recruitment rates compared across sites in terms of how many recruited, who is recruited and also how quickly people are recruited
	• Comparison of potentially eligible women with those recruited using data from case report forms and screening forms
	• Recruitment issues explored in the staff focus groups and participant interviews
Retention	• Dropout by trial arm
	• Dropout by site
	• Comparison of demographics of those dropping out with those remaining
Contamination	• Participants asked what other services control group utilised in case report forms
	• Contamination explored in the staff focus groups and participant interviews
Theory testing	• Mediation analyses using questionnaire data
	• Theoretical mediators explored in the staff focus groups and participant interviews

A key method for assessing these components is via the qualitative data collection i.e. qualitative interviews with participants and focus groups with the staff delivering the intervention. Semi-structured interviews will be completed with approximately 30 participants from the intervention group, purposively sampled across sites according to attendance levels at the intervention group sessions and whether they lost weight or not. The interviews will be carried out at the end of the intervention period (at approximately 6 months postpartum) and at the end of the study (at approximately 12 months postpartum). We will explore the participants’ views of the intervention, barriers and facilitators, the impact of life events on adherence to the intervention, importance of social support, strategies, coping mechanisms and responses to relapses. We will interview a small sample of participants who drop out of the intervention but who are willing to be interviewed, to establish their views of the intervention and reasons for discontinuing. We will also conduct brief interviews with a sample of around 15 women from the control group about taking part in the study and any lifestyle changes they made both during and after pregnancy. The interviews will continue until data saturation is reached.

Three intervention staff focus groups will be completed and will explore the intervention components, the delivery of the intervention, intervention fidelity, participant adherence to the intervention, the recruitment process, perceived challenges or barriers in implementing the intervention and potential improvements to the intervention or the training.

With regards to theory testing we developed a logic model (this is shown in Figure 1) to explain the processes by which the intervention brings about change and we plan to test the theory of our intervention via mediation analyses as well as through other aspects of the process evaluation including participant interviews. Potential mediators including self-regulation, intrinsic motivation, self-efficacy and social support will be assessed. The analyses will identify both the extent to which the intervention was successful at changing these mediators and the extent to which mediator change was associated with change in BMI. Potential moderators of intervention effect will be examined including demographics, ethnicity, parity, mental health (also an outcome), smoking status and weight loss history.

### Economic evaluation

The main evaluation will be a cost utility analysis assessing between group differences in total costs against differences in Quality Adjusted Life Years (QALY) derived from the EQ-5D quality of life instrument [88]. This approach is preferred by the National Institute for Health and Care Excellence (NICE) for the economic evaluation of NHS interventions as resulting cost utility estimates can be compared across unrelated health care interventions (http://www.NICE.org.uk). However, as a generic measure, EQ-5D may not be sufficiently sensitive to capture small changes in health-related quality of life in essentially healthy participants. A secondary cost effectiveness analysis will therefore be undertaken with BMI as the effectiveness measure. Both analyses will be done from an NHS perspective but as the HELP intervention might substitute for other weight control interventions, patient borne costs will also be assessed but will be reported separately.

Resources for training intervention midwives and delivery of the intervention will be recorded prospectively in relevant units and valued using standard methods [96]. Participants’ use of NHS resources will be collected by questionnaire from women in both arms of the trial at baseline and all follow-up points specified above and similarly valued. The questionnaire will also record payments for non-NHS weight loss/maintenance activities and will include the EQ-5D questionnaire [88].

### Analysis

#### Quantitative analysis

The main analysis will be by intention to treat and will compare the primary outcome of BMI at 12 months postpartum in the intervention and control groups. Multilevel modelling will be used to account for clustering within antenatal unit and individual effects. A two level linear regression model will include baseline BMI (measured at recruitment) as a covariate. Both levels will be considered ‘random effects’ i.e. patients and units are drawn randomly from a larger population of patients and units. Cluster level variables include those used to balance the randomisation: antenatal unit size; proportion of women with BMI +/=30, geographic location and ethnic mix.

For the BMI data, positively skew distributed form is anticipated and will be checked prior to analysis. Log transformation will be considered, not only to deal with the non-normality but to allow interpretation of differences between arms in percentage terms. To further aid clinical interpretation of the intervention effect, analysis of log transformed weight at 12 months postpartum will also be considered, with baseline log weight and log height as covariates. The results can then be expressed in terms of BMI or weight along with a 95% confidence interval. The intra-cluster correlation (ICC) for the primary outcome will be calculated and reported.

Intention to treat analysis will be used for all secondary outcomes. Analysis of secondary outcomes will also use multilevel modelling incorporating baseline scores as covariates where appropriate. Two level linear regression models will be used for outcomes such as pregnancy weight gain and waist-to hip ratio and validated questionnaire scores, while logistic models will be used for clinical event outcomes. 95% confidence intervals for the intervention effect will be calculated. The ICC for each secondary outcome will be calculated and reported.

The impact of individual demographic factors as well as theoretical mediators (self-efficacy, social support, intrinsic motivation and self-regulation) on the intervention effect using interaction terms included in the main analysis models will be examined. Individual demographic variables include age, ethnicity, smoking status, previous weight loss history, psychological wellbeing and social class. We also intend to carry out tests for mediator variables [97].

As well as examining number of sessions attended, patterns of missed sessions and compliance with the intervention will also be explored. A complier average causal effect (CACE) analysis will be carried out for the primary outcome to assess the effect of the intervention in those who complied [97,98]. An investigation of required minimum dose of intervention will be carried out. A per- protocol analysis will include only those participants in each arm that received treatment as randomised excluding those in the control arm attending weight loss groups.

No formal subgroup analyses are planned. However, exploratory analyses of the impact of social class, parity, ethnicity (if numbers permit), smoking status and initial BMI on the effect of the intervention will be carried out. This will be achieved by fitting a subgroup by randomised group interaction term to the multilevel model.

If the proportion of missing primary data is substantial (more than 10%) a series of sensitivity analyses will be carried out to determine the likely effects of missing data [99-101]. The intention is to use multiple imputation to generate complete datasets for analysis. Imputation models will include those variables in the analytic model plus any additional variables associated with missingness and outcome. Self-reported weight (from the minimum dataset) and Slimming World session weight data may be used to replace missing weights where appropriate in secondary analyses. Further sensitivity analyses may be carried out to examine the effects of removing women who are known to be pregnant at the 12 month postpartum follow-up, as well as those who have recently given birth to a second baby. The assumptions of all models used for primary and secondary analysis will be checked.

Short and long term effects of the intervention can be examined using repeated measures analysis of intermediate weight measurements. The difference in weight at 6 months postpartum will also be examined. The proportion of participants who lost 5% of their weight (weight at 6 months postpartum compared to baseline) will be calculated for each arm. The difference between groups will be examined to identify if they maintained that loss. The association between subsets of clinical outcomes will also be investigated and a total count of all clinical outcome events will be calculated and compared between trial arms. Individuals lost to follow-up will be compared to those who complete follow-up to identify potential sample bias.

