### Sample size

At the time we were developing the study we could find no systematic reviews of lifestyle interventions in pregnant women, so we based our sample size on a systematic review of interventions with obese adults, which found a mean weight loss of 7.9 kg (8.5%) during the first 6 months of interventions involving diet and exercise, after which weight was gradually regained, by 48 months a mean weight loss of 3.9 kg (4%) was maintained [28]. Results for trials which included only obese women (mean BMI+/=30 at baseline) demonstrated weight loss of a similar magnitude at 12 months [28]. In order for an individually randomised trial to have 80% power to detect a moderate effect size of 0.333 for a difference in BMI at 12 month follow-up of 1.5 kg/m^2^ (SD = 4.5), at a 5% significance level, 143 women per group would be required. Little pertinent data are available for the estimation of the intra-cluster correlation coefficient (ICC). Assuming an ICC of 0.02, if 20 maternity units were recruited across England and Wales, a variance inflation factor of 1.4 would result, so the total sample size is therefore inflated to 400 to detect the difference stated above and we would require an average of 20 women per unit. This would allow for a variance inflation factor of 1.4 (ICC = 0.02) [73]. In trials investigating weight management interventions in pregnant women, losses to follow-up range considerably from 5% to 38% [58,59,74-76], therefore we have allowed for a drop out of 30% and intend to recruit 570 women.

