### Participant recruitment

570 pregnant women with a Body Mass Index (BMI) of +/=30 aged 18 years or older and between 12 and 20 weeks gestation will be recruited. Potentially eligible participants will be approached at their earliest antenatal appointment by NHS midwives or researchers, who will provide an information sheet and briefly describe the study. The decision to approach women will not be made by the midwife delivering the intervention. If women are eligible and interested in participating, they will be contacted by the research midwife (local Principal Investigator (PI)) to discuss the study in greater detail and arrange a baseline home visit where informed consent and baseline measures will be taken.

The approaching midwife/researcher will provide the women with a comprehensive information sheet prior to the baseline visit and adequate time will be given for them to read the material and to ask any questions they have about the study. Women will be reminded that they retain the right to withdraw consent for participation in any aspect of the trial at any time without their routinely available NHS care being affected. Midwives/researchers will be trained in Good Clinical Practice and all study procedures. The participant’s GP, named midwife and obstetrician, if applicable, will be informed that she is taking part in the study.

A screening form will be completed to record the number of women approached about the study, eligibility, and at what stage women declined to take part in the study (e.g. when first approached or at the consent stage).

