**Primary outcome**		
Maternal weight expressed as BMI relative to height measured at baseline	Calibrated adult scales & stadiometer	B, 36w, 6p, 6 m, 12 m

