**Secondary outcomes**		
Antenatal and birth complications**	Routinely collected data held in patient records	Birth
Pregnancy weight gain	Calibrated adult scales	B, 36w
Waist circumference and waist-hip ratio	Measuring tape	12 m
Child weight centile (adjusted for birth weight and age)	Calibrated baby scales and measuring tape	Birth, 6p, 6 m, 12 m
Admission to neonatal unit	Patient records	Birth
General mental health	General Health Questionnaire (GHQ) 12 [82]	B, 36w, 6p, 6 m, 12 m
Breast feeding intentions	Study-developed questions	36w
Breast feeding behaviour and weaning	Study-developed questions	6p, 6 m, 12 m
Self-reported physical activity	7 Day Physical Activity Recall (7 Day PAR) [83-85]	B, 36w, 6p, 6 m, 12 m
Diet	Dietary Instrument for Nutrition Education (DINE) [86] (plus additional questions on fruit and vegetables, sugar, sweets)	B, 36w, 6p, 6 m, 12 m
Alcohol	Alcohol Use Disorders Identification Test-Consumption (AUDIT-C) [87]	B, 36w, 6p, 6 m, 12 m
Smoking	Study-developed questions	B, 36w, 6p, 6 m, 12 m
Costs	Participant resource use	B, 36w, 6p, 6 m, 12 m
Health related quality of life	EQ-5D (including visual analogue scale) [88]	B, 36w, 6p, 6 m, 12 m

*B = baseline; 36w = 36 weeks gestation; 6p = 6 weeks postpartum; 6 m = 6 months postpartum; 12 m =12 months postpartum.

**gestational diabetes; pre-eclampsia; thrombosis; proportion staying within IOM guidance on weight gain in pregnancy [20]; form of pain relief; birth delivery mode; gestation at delivery; induction of labour; shoulder dystocia, 3^rd^/4^th^ degree perineal tear; postpartum bleeding or thrombosis; Apgar scores.

**Table 2 T2:** Measurement of Mediators

**Mediators**	**Measure**	**When**
Social support	Social Support Exercise and Eating Habits Scales [89] (plus intervention specific social support questions)	B, 36w, 6 m, 12 m
Self-efficacy	Weight Efficacy Lifestyle Scale [90] and Multidimensional Self efficacy for Exercise Scale [91,92]	B, 36w, 6 m, 12 m
Self-regulation	Shortened Self-Regulation Questionnaire [93]	B, 36w, 6 m, 12 m
Motivation	Treatment Self-Regulation Questionnaire (for diet and physical activity) [94]	B, 36w, 6 m, 12 m

(B = baseline; 36w = 36 weeks gestation; 6 m = 6 months postpartum; 12 m =12 months postpartum).

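### The covariate rule for secondary outcomes supplies nothing for waist circumference and waist-hip ratio, which have no baseline value; baseline BMI is collected and should be named as their covariate

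*Protocol article*

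**What the plan says.** Table 1 of the protocol article (Secondary outcomes) has the row "Waist circumference and waist-hip ratio Measuring tape 12 m". No baseline waist or hip measurement is listed. The primary outcome row, "Maternal weight expressed as BMI relative to height measured at baseline", is scheduled at baseline and at all four follow-ups. Under Participant recruitment, the research midwife is to "arrange a baseline home visit where informed consent and baseline measures will be taken", so each recruited woman should have a baseline BMI.

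Under Quantitative analysis, the primary model is specified thus: "A two level linear regression model will include baseline BMI (measured at recruitment) as a covariate". For secondary outcomes the rule is "Analysis of secondary outcomes will also use multilevel modelling incorporating baseline scores as covariates where appropriate". The text continues: "Two level linear regression models will be used for outcomes such as pregnancy weight gain and waist-to hip ratio and validated questionnaire scores". Waist-hip ratio is therefore named as an outcome for this class of model, but no covariate is named for it. Waist circumference is not mentioned separately in the analysis section.

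**The concern.** The rule calls on a baseline score, and the waist outcomes have none. Elsewhere in the same section, when a covariate other than the outcome's own baseline is wanted, it is written down: log height is added to baseline log weight in the supplementary weight analysis. Nothing comparable is written for waist.

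Two things are at stake, both modest. The first is precision: baseline BMI is likely to be related to later waist size, and leaving it out forgoes a reduction in residual variance. The second is comparability between arms. Allocation is balanced on the proportion of each unit's pregnant population with a BMI of 30 or more, together with region, unit size and ethnic mix. That does not control how obese the recruited women are, since all of them are at or above 30. With 20 units, the arms can differ by chance in mean baseline BMI. The primary analysis adjusts for such a difference; a waist analysis without baseline BMI would not.

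**Working it through.** **Inputs from the Sample size section.** Difference 1.5 kg/m², SD 4.5 (0.333 SD), 80% power, 5% significance (two-sided assumed), 143 women per group, ICC 0.02, 20 units, 20 women per unit, 400 analysed, 30% dropout, 570 recruited. Allocation is 10 units to 10 (Abstract).

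**The plan's own figure.**
- The t-test calculation with d = 0.333 gives 142.5, hence 143 per group, or 286 in all.
- The design effect is 1 + (20 − 1) × 0.02 = 1.38, rounded in the article to 1.4. Then 286 × 1.38 = 394.7 and 286 × 1.4 = 400.4.
- 400 / 0.70 = 571.4, so 572 against the stated 570.

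The sample size reproduces. It concerns BMI only; the article states no power for the waist outcomes.

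**Assumptions added here.** The waist outcomes are given the same ICC (0.02) and the same 400 analysed women. The correlation r between baseline BMI and the 12-month waist measure is not in the article, so a range is shown.

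**Standard error of the arm difference, in SD units, with 10 units and 200 women per arm.**
- No baseline covariate: √[2 × (0.02/10 + 0.98/200)] = √0.0138 = 0.1175.
- BMI explains variance at both levels: √[0.0138 × (1 − r²)].
- BMI explains within-unit variance only: √{2 × [0.02/10 + 0.98 × (1 − r²)/200]}.

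The detectable difference at 80% power is (1.96 + 0.84) × SE, which is 0.329 SD with no covariate.

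| r (assumed) | SE, within units only | SE, both levels | Fall in SE | Detectable difference (SD) |
|---|---|---|---|---|
| 0.3 | 0.1137 | 0.1121 | 3–5% | 0.318–0.314 |
| 0.6 | 0.1014 | 0.0940 | 14–20% | 0.284–0.263 |
| 0.8 | 0.0868 | 0.0705 | 26–40% | 0.243–0.197 |

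For example, at r = 0.6 within units only, the variance is 2 × (0.002 + 0.0049 × 0.64) = 0.01027. Its root is 0.1014, and 0.1014/0.1175 = 0.86.

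**Chance imbalance.** Taking SD 4.5 and ICC 0.02 for baseline BMI as well, one standard error of the between-arm difference is 4.5 × 0.1175 = 0.53 kg/m². An imbalance of that size carries r × 0.1175 SD into an unadjusted waist comparison: 0.035 SD at r = 0.3 and 0.094 SD at r = 0.8. This should not be added to the precision loss. It is the same variance, seen from within one realised allocation.

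**The case against.** A reader might infer that the protocol commits to an unadjusted comparison of the waist outcomes. It does not. The rule does not restrict the baseline score to the outcome's own, its closing qualifier leaves room for judgement, and the sentence refers back to a primary model whose covariate is baseline BMI. The article nowhere says that the waist outcomes go unadjusted or that baseline BMI may not be used. Covariates for individual secondary outcomes are also commonly left to an analysis plan, which is not shown. All of this stands, and it rules out calling the text an error or a contradiction.

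It is also true that a two-level comparison without a baseline covariate is valid under randomisation and accounts for clustering. Allocation is drawn from the 25% best-balanced in each block, and the balancing variables are listed as cluster-level variables in the analysis, though it is unclear whether that extends to the secondary models. These features help with unit-level balance. They do not act on differences in BMI among the women recruited.

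The size of the gain can fairly be challenged. Every r is assumed. Restricting entry to a BMI of 30 or more narrows the range of BMI and tends to lower r, as does the gap of more than a year between a measurement at 12 to 20 weeks' gestation and one at 12 months postpartum. The simple factor √(1 − r²) also holds only if BMI explains between-unit variance as well as within-unit variance. Nor should the gain be restated as a multiple of the number of women, because with 20 fixed units extra women per unit leave the between-unit component unchanged. These objections lower the expected size without removing the point.

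**Conclusion.** The point holds as a low-cost improvement to the analysis of two secondary outcomes. As written, the rule supplies no individual-level covariate for waist circumference or waist-hip ratio, and the obvious substitute, already collected and already in the primary model, is not named.

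The size rests on the assumed r, an ICC of 0.02 and 400 women analysed. For waist-hip ratio, where r of about 0.3 is plausible, the standard error falls by only 3–5%. For waist circumference, r between 0.6 and 0.8 would give 14–20% to 26–40%, the lower figure in each pair applying if BMI acts within units only. The upper end is optimistic given the entry criterion.

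The documents do not support the stronger reading that the waist results would be biased or invalid. The primary analysis and the sample size are unaffected.

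**What to change.** Add one sentence to the secondary-outcome analysis: waist circumference and waist-hip ratio, having no baseline measurement, will be adjusted for baseline BMI as an individual-level covariate in the two-level linear model, as in the primary analysis.

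This needs no new data or visits and costs one individual-level degree of freedom. If it is fixed before outcome data are seen, it also prevents the choice between an unadjusted and a BMI-adjusted waist comparison from being made with the results in view.
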